## Abstract

**Background:**

Psychiatric nurses are aware of the importance of the therapeutic relationship in psychiatric units. Nevertheless, a review of the scientific evidence indicates that theoretical knowledge alone is insufficient to establish an adequate therapeutic alliance. Therefore, strategies are required to promote changes to enhance the establishment of the working relationship. The aims of the study are to generate changes in how nurses establish the therapeutic relationship in acute psychiatric units, based on participative action research and to evaluate the effectiveness of the implementation of evidence through this method.

**Methods/Design:**

The study will use a mixed method design. Qualitative methodology, through participative action research, will be employed to implement scientific evidence on the therapeutic relationship. A quasi-experimental, one-group, pre-test/post-test design will also be used to quantitatively measure the effectiveness of the implementation of the evidence. Participants will consist of nurses and patients from two psychiatric units in Barcelona. Nurses will be selected by theoretical sampling, and patients assigned to each nurses will be selected by consecutive sampling. Qualitative data will be gathered through discussion groups and field diaries. Quantitative data will be collected through the Working Alliance Inventory and the Interpersonal Reactivity Index. Qualitative data will be analysed through the technique of content analysis and quantitative data through descriptive and inferential statistics.

**Discussion:**

This study will help to understand the process of change in a nursing team working in an inpatient psychiatric ward and will allow nurses to generate knowledge, identify difficulties, and establish strategies to implement change, as well as to assess whether the quality of the care they provide shows a qualitative improvement.

## Background

The Therapeutic Relationship (TR) is one of the most important tools at nurses’ disposal, especially in mental health nursing. Indeed, the concept of the therapeutic relationship emerged in parallel to the professionalization of nursing care [1] and is considered the cornerstone of psychiatric and mental health nursing [2]. Adequate establishment of the therapeutic relationship increases the efficacy of any nursing intervention in the acute mental health setting [3].

Multiple terms are used to describe the same concept. The TR is also called the helping relationship, the nurse-patient relationship, the trusting relationship, and the therapeutic alliance. Nevertheless, the central focus of all these concepts is the helping working relationship [4]. Likewise, the concept of the TR has been enriched by diverse perspectives and paradigms, including the psychodynamic perspective originating with Freud, the pantheoretical model, and the humanist or person-centred approach. Consequently, some authors have stated that personal qualities rather than theoretical orientation take centre stage in the TR [4].

Psychiatric nurses are aware of the concept of the TR and its importance [2, 4–10]. However, they are also aware that specific skills are required to develop and maintain a TR with patients [7], which involves a huge effort and, moreover, implies difficulty in its achievement. Factors such as consistency, empathy, the ability to listen, making a positive first impression, a safe and comfortable environment, and teamwork are basic pillars, encouraging and aiding the development of a TR [10].

For their part, patients perceive attitudes, values and a trusting relationship as being more important than technical skills in the therapeutic relationship [4]. Service users expect to receive individual attention as part of their treatment plan [11]. Having a feeling of control and of self-determination is highly important, and this sense of meaning and control is provided by interpersonal relationships [12]. So much so, that what patients want most are empathetic nurses, ie, those able to identify what the patient expects or needs from the nurse at any given moment [4]. Patients value nurses who are patient and imaginative and have a sense of humour [9], who listen and are empathetic [4]. The greater the chronicity, the more patients lose interest in their physical needs and the more they value relational aspects of care [13].

Despite evidence of the greater effectiveness of the TR and psychodynamic training in clinical practice [14], mental health nursing has been strongly influenced by the biomedical model and has become increasingly depersonalized [15]. There is no recognition of the need for the care of emotions, or of the importance of the emotional work required to develop and maintain a quality TR [13]. In this regard, routine tasks and administrative duties, as well as the time they consume, hamper the provision of individual attention and consequently the effectiveness of the TR [11]. Nevertheless, some evidence suggests that staff spend increasingly less time with patients, despite an increase in the staff-to-patient ratio in some units [16].

For some patients, inaccessibility and lack of communication-and therefore a lack of information provided by some staff-are factors that limit the TR [17]. Likewise, lack of availability, inequality, and differences in values and experience are factors that distance nurses from patients and hamper the development and maintenance of the therapeutic alliance. Often, patients feel they are given little opportunity to collaborate in their care [17], perceive that they spend most of their time alone and that they have little relationship with the care team [16]. Some patients feel like prisoners and report that staff who are themselves insecure adopt intimidating and condescending attitudes [18].

According to nurses, the elements that most frequently hamper the therapeutic relationship are the amount of time spent on administrative duties, patients’ negative attitudes and unrealistic expectations, nurses’ inability to confront these issues with patients, and feeling inadequately trained to provide the individual attention required by patients [11]. Also important are nurses’ perception that socially unacceptable factors such as segregation, coercion and social control are working norms and that this situation is, moreover, experienced as demotivating and routine, as if working life were dominated by functions of social control [19].

In this regard, and although nurses are aware of the importance of the TR and how to foster such an alliance, the scientific evidence shows that theoretical knowledge of communicative and interpersonal skills alone is insufficient to develop these skills effectively, and hence to establish an effective therapeutic relationship and provide high-quality nursing care [3, 9, 15–17, 20–23].

Therefore, if knowledge of these skills does not necessarily lead to their use in daily clinical practice, it seems necessary to devise strategies to promote these competencies. Effecting change *for* action and *through* action is characterised by participation and reflection, which encourages both learning through action and about the action taking place.

### Theoretical framework

Participatory Action Research (PAR) is a method that encourages participatory and reflective change at the same time as it increases an understanding and transformation of practices [24]. Thus, PAR aims to achieve reliable, effective and efficient results to improve group or collective situations. PAR is a research method because it aims to increase knowledge and understanding of phenomena through exploratory scientific techniques. Moreover, PAR is also an action because it aims to intervene in the phenomenon being explored by effecting change in that phenomenon. Finally, PAR is participatory since it encourages collaboration and cooperation among all the persons involved throughout the process.

Therefore, PAR is a dynamic method consisting of an open, holistic and egalitarian process among researchers and participants [25]; the action needs to be filtered through experience and reflection before it can improve or change practices. In PAR, knowledge generation is viewed as a collaborative process, in which the skills and experiences of each participant are essential to the outcome of the project. The goal of PAR is to resolve or modify specific problems in communities, in this case, in acute care nursing teams. The process is effected through a series of steps included in a spiral of self-reflective circles (Fig. 1): 1. Planning a change, 2. Acting and observing the process of change, 3. Reflecting on the process and its consequences, 4. Replanning, 5. Acting and observing again, 6. Reflecting again … and so on [24].

**Fig. 1 Fig1:**
[figure not shown]
Stages of Participatory Action Research

### Objectives

General:To generate change in how nurses establish the therapeutic relationship in an acute psychiatric unit, based on PAR.To evaluate the effectiveness of the implementation of scientific evidence through PAR, in terms of improving the therapeutic relationship, as perceived by nurses and patients, and enhancing empathy, as perceived by nurses.

Specific:To describe how nurses in an acute psychiatric unit perceive the establishment of the therapeutic relationship with patients.To identify nursing professionals’ difficulties and limitations when establishing a therapeutic relationship with a patient.To identify the elements of change and improvement in the establishment of the therapeutic relationship, based on contrasting the evidence with real-world clinical practice.To qualitatively evaluate the effects of the implementation of evidence on the development of the therapeutic relationship between nurses and patients.To analyse the impact of the implementation of scientific evidence on the establishment of the therapeutic relationship on:Measurement of the therapeutic relationship, evaluated by staff before and after the PAR process.Measurement of the therapeutic relationship, evaluated by patients before and after the PAR process.Measurement of empathy, evaluated by staff before and after the PAR process.

## Methods/Design

### Study design

An overall design for the research project is proposed, following a mixed sequential transformational method [26]. The qualitative method will guide the process and will be the central axis of the design. Nevertheless, the sequential use of quantitative methods during the study will serve to control the process [24] and will complement analysis of the results (Fig. 2).

**Fig 2 Fig2:**
[figure not shown]
Study design

Therefore, to achieve the first objective, a qualitative design will be used in the form of PAR, within the constructivist paradigm and following the model of Kemmis and McTaggart [24] in cycles and stages. PAR is a method that integrates research and social action [25] and, during its implementation, includes the following stages: a) analysis of the situation, b) identification of problems and design of strategies for the proposed action, c) implementation of the strategies designed, and d) observation and systematic reflection on their implementation.

To achieve the second objective, a quasi-experimental study of a single pre-test/post-test group is proposed, with evaluation of the implementation of the evidence through PAR [27].

### Setting and participants

The study will be conducted in the acute psychiatric admissions ward of the Institute of Neuropsychiatry and Addictions (*Institut de Neuropsiquiatria i Addiccions* [INAD]) of Parc de Salut Mar de Barcelona (Spain): the Institute consists of 4 units with 107 in-patient beds for patients with acute psychiatric disorders. These units cover a population of approximately 650,000 inhabitants in the City of Barcelona, Badalona and Santa Coloma de Gramanet.

Study participants will consists of nurses working in the acute-stay units and patients admitted to these units. Theoretical sampling will be carried out in nurses. The sample will be composed of 9–10 participants representing the distinct socio-occupational profiles in the units. Thus, the group will be composed of nurses from each of the three shifts, by specialist and generalist nurses, and by staff and supply nurses. The aim is to guarantee the principles of heterogeneity and accessibility [28].

We estimate that about 30 patients will be allocated to each participating nurse in the phase prior to the start of the groups, and consequently, accepting an alpha risk of 0.05 and a beta risk of 0.2 in the bilateral contrast, nine participants will be needed to detect a difference equal to or higher than 10 units in the Working Alliance Inventory-Short (WAI-S). A standard deviation of 10 will be accepted, and a loss to follow-up rate of 10%. Consecutive sampling will be performed. Inclusion criteria will consist of the following: a) Being assigned to a participating nurse, b) Having established a link with the participating nurse during a hospital stay longer than 3 days, b) voluntarily accepting to participate in the project and providing signed informed consent.

Exclusion criteria will consist of a) showing signs of the initial stages of psychomotor agitation, and b) being subjected to physical restraint, either currently or within the last 24 h.

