### Limitations

The duration and intensity of the research is a factor to be considered, as some participants may be lost. Therefore, it was decided to increase the size of the group sample. In addition, difficulties may appear that are specific to discussion groups, such as differences among the functioning of the groups, or limitations related to the reflective diaries, such as irregular entries or subjective interpretations by participations of situations that are foreign to their experience. The strategies that will be used to minimize difficulties and limitations are as follows: the use of known but neutral spaces to hold the groups, avoidance of simultaneous note-taking, placement of the recording device in a barely-visible area, and a priori determination of the maximum duration of the group session. The group interviewer and facilitator will be an expert in individual and group interviews and trained in communication skills. Participants will also be given documented tools to help them keep a reflective diary. Other limitations concern those inherent to a quasi-experimental design, such as the lack of a control group and the non-randomization of the sample.

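### Nine participants do not give the stated 80% power with the planned paired t-test: the plan's own inputs give about 68% after the 10% loss and 75% with no loss.

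*Protocol article*

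**What the plan says.** Setting and participants fixes all the inputs. The error rates are given as "accepting an alpha risk of 0.05 and a beta risk of 0.2 in the bilateral contrast". The target and the result come together: "nine participants will be needed to detect a difference equal to or higher than 10 units in the Working Alliance Inventory-Short (WAI-S"). The remaining inputs follow: "A standard deviation of 10 will be accepted, and a loss to follow-up rate of 10"%. For the nurses, the same section says "The sample will be composed of 9–10 participants".

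Study design specifies a single group measured before and after the intervention. Quantitative data analysis names Student's t-test for paired data for quantitative variables, with the Wilcoxon test if the data are not normal. Limitations mentions possible loss of participants and adds "Therefore, it was decided to increase the size of the group sample", but gives no number, so 9–10 is the only sample size stated.

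**The concern.** With eight or nine pairs, the sizing formula has to match the test. The usual normal formula treats the SD as known. The paired t-test estimates it from the same few pairs and pays with a larger critical value: 2.36 at 7 degrees of freedom and 2.31 at 8, against 1.96. A figure of nine for an effect of one SD, with loss already included, looks like the normal formula applied where it is too optimistic.

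The stated beta governs how a null result is read. Evaluating the effectiveness of the implementation is one of the two general objectives, and the Discussion expects the instruments to help demonstrate change. If power is really about 70%, a non-significant result is weaker evidence against a 10-unit improvement than a reader of the protocol would believe.

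**Working it through.** **Inputs**

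| Input | Value | Source (protocol article) |
|---|---|---|
| Alpha | 0.05, two-sided | Setting and participants |
| Beta | 0.2 (power 80%) | Setting and participants |
| Difference | 10 WAI-S units | Setting and participants |
| SD | 10 (type not stated) | Setting and participants |
| Loss | 10% | Setting and participants |
| Stated n | 9; planned nurses 9–10 | Setting and participants |
| Test | paired t-test | Quantitative data analysis |

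**Step 1. Reproduce the nine.** Normal formula for paired data, with 10 as the SD of the change:

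n = (z₀.₉₇₅ + z₀.₈₀)² × (SD/difference)² = (1.960 + 0.842)² × (10/10)² = 7.85, rounded up to 8.

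Allowing for loss: 8/(1 − 0.10) = 8.9, rounded up to **9**. This is the stated figure. Under the normal formula, 8 completers have 80.7% power.

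**Step 2. Power of the planned test.** Two-sided paired t-test, noncentral t distribution with n − 1 degrees of freedom and noncentrality √n × 10/10 = √n:

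| Completers | Normal formula | Paired t-test | Change detectable with 80% power (t-test) |
|---|---|---|---|
| 8 | 80.7% | **68.1%** | 11.6 units |
| 9 | 85.1% | **74.8%** | 10.7 units |
| 10 | 88.5% | 80.3% | 10.0 units |

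**Step 3. Power with the planned loss.** If each participant is lost independently with probability 10%, average t-test power is 68% with 9 recruited and 74% with 10 recruited.

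**Step 4. Size the t-test would need.** Ten completers are the fewest that reach 80%. Allowing for loss: 10/0.9 = 11.1, rounded up to 12 recruited.

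**Step 5. Sensitivity to the meaning of the SD.** If 10 is the SD of a single score and r is the pre–post correlation, the SD of the change is 10 × √(2(1 − r)). The document gives no r, so these values are assumptions:

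| r | SD of change | Power, 8 completers | Power, 9 completers |
|---|---|---|---|
| 0 | 14.1 | 40.8% | 46.3% |
| 0.3 | 11.8 | 54.0% | 60.5% |
| 0.5 | 10.0 | 68.1% | 74.8% |
| 0.6 | 8.9 | 77.4% | 83.5% |
| 0.7 | 7.7 | 87.7% | 92.2% |

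**Step 6. The fallback test.** The exact two-sided Wilcoxon signed-rank test, simulated with normal data and the same effect, gives about 61% power with 8 pairs, 68–69% with 9 and 78–79% with 10. It does not recover the loss.

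**The case against.** Four points can be made for the plan.

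- **The SD is not defined.** If 10 is the SD of a single score, the shortfall disappears once the pre–post correlation reaches about 0.6–0.65. That is true, but lower correlations make it worse, and the protocol states none. The SD-of-change reading, or the equivalent correlation of 0.5, is the one that gives exactly nine. This point limits certainty about the size of the shortfall; it does not restore the stated 80%.
- **The unit is not spelled out.** The section links the nine to about 30 patients per nurse, so the analysed score might be a nurse's mean over patients. That stands as an ambiguity. But neither the stated inputs nor the analysis section uses the patients, with no averaging step and no intraclass correlation, and nine is reproduced without them. The power figures here are those of the nine-participant calculation as written.
- **It is not a slip of arithmetic.** Agreed. The sums are right for the normal formula; the fault is that the formula does not match the named test at this sample size.
- **The study is mainly qualitative, and Limitations says the group was enlarged.** The qualitative work is indeed the central element, and nurses are chosen for heterogeneity. This lowers the consequence, but the power claim is still made. Limitations gives no number larger than the 9–10 already stated, and ten nurses reach 80.3% only if none is lost.

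**Conclusion.** The concern holds. On the plan's own inputs, nine participants give 68.1% power after one loss and 74.8% with none, which is 12 and 5 percentage points below the stated 80%. The true beta is about 0.25–0.32. Recruiting ten, the top of the planned range, gives 74% on average after 10% loss.

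This rests on two assumptions: that 10 is the SD of the within-participant change, and that each participant contributes one pair of scores. Both follow from how nine is obtained, but the protocol states neither. If the SD is that of a single score, power at 8–9 completers runs from 54–61% at a correlation of 0.3 to 88–92% at 0.7.

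**What to change.** Under Setting and participants, replace the statement that nine are needed with what the design provides. For example: with 9–10 nurses and 10% loss (about 8–9 completers), the two-sided paired t-test at the 0.05 level has about 68–75% power to detect a 10-unit WAI-S change when the SD of the change is 10, or 80% power for a change of about 10.7–11.6 units.

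In the same place, state that 10 is the SD of the within-participant change. If the authors meant the SD of a single score, they should say so, give the assumed pre–post correlation and recompute.

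The cost is a sentence or two and a less favourable power figure. The sample, the test and the conduct of the study can stay as they are. Keeping the 80% claim for 10 units would instead need 10 completers, or 12 recruited at 10% loss; the correction does not require that.

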### Qualitative data collection

Qualitative data will be generated through discussion groups and field diaries kept by participating nurses and researchers.

### Discussion groups

Due to the importance of team work and the consequent collective social discourse distinct from individual discourse [29], it is useful for nurses to debate the objectives of the research as a group. Four group sessions will be held to cover the distinct PAR stages.

### Reflective diary

Participating nurses will construct a narrative of their own observations of the establishment of the therapeutic relationship with patients and will conduct a reflective analysis of these observations [30]. To help aid self-observation and subsequent reflection, the nurses will be provided with a dossier-guideline specifying how to conduct the self-observation and subsequent reflection.

The researcher’s field diary will help to monitor the research process [31], both descriptively and methodologically, and will help to integrate theory and practice.

### Quantitative variables and data collection

The following variables and measurement instruments will be used for quantitative data.

Variables:Sociodemographic and occupational variables in nurses, and sociodemographic and clinical variables in patients.Dependent variablesThe nurse-patient relationship, from the nurse’s perspective, evaluated through the WAI-S scale, therapist version [32].The nurse-patient relationship, from the patient’s perspective, evaluated through the WAI-S scale, client version [32].Nurse empathy, from the nurse’s perspective, measured with the Interpersonal Reactivity Index [33].
Independent variables:Implementation of evidence through PAR.

Instruments:The Working Alliance Inventory (WAI short). This inventory measures the working alliance and therefore the nurse-patient relationship (Horvath & Greenberg 1989). The short version of this scale contains 12 items, and each item is evaluated by the health professional and patient through a scale ranging from 1 (never) to 7 (always). The higher the score, the greater the therapeutic alliance. The Spanish version of the WAI-S has good reliability and validity, with a Cronhbach’s alpha of .91 [34].The interpersonal reactivity Index (IRI). The most important element in establishing the therapeutic relationship is possibly empathy. For this reason, empathy will be specifically measured through the instrument designed by Davis [33]. This index has 28 items in a Likert scale (1 = not good at all and 5 = very good). Crohnbach’s alpha for the Spanish version ranges from .73 to .71 among the 4 factors composing the IRI [34].

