#### Quantitative data analysis

The analysis will focus on numerical differences, obtained in the WAI-S and IRI, observed before and after the group phases of the PAR. Descriptive statistics will be used for sample description and evaluation of the scores. Differences between baseline scores and the post-group assessment will be estimated through the application of a parametric test (Student’s *t*-test for paired data) in the case of quantitative variables after confirmation of the normality and homogeneity of their variance; for data that do not follow a normal distribution), non-parametric tests will be used: the Wilcoxon test will be used for quantitative variables and the chi-square test or Fisher’s exact test for qualitative variables. To interpret the results, statistical significance will be set at *p* < 0.05 for a 95% confidence interval (95% CI) in the case of a bidirectional hypothesis. The analysis will be performed with the IBM SPSS Statistics 21 package.

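### The paired WAI-S test carries no patient covariates, so a change in each nurse's patients or in day of stay between phases can be read as a PAR effect

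*Protocol article*

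**What the plan says.** All references are to the protocol article.

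- **Patients.** *Setting and participants* expects that "about 30 patients will be allocated to each participating nurse in the phase prior to the start of the groups", and adds: "Consecutive sampling will be performed". A patient must have been in hospital for more than 3 days and have formed a link with the nurse. No upper limit or fixed day is given for completing the WAI-S. The patients rated after the groups are not described.
- **Nurses.** The same section says: "The sample will be composed of 9–10 participants representing the distinct socio-occupational profiles in the units". It bases the sample size on a 10-unit WAI-S difference, an SD of 10 and 10% loss, "accepting an alpha risk of 0.05 and a beta risk of 0.2 in the bilateral contrast", and arrives at nine participants.
- **Variables.** *Quantitative variables and data collection* lists "sociodemographic and clinical variables in patients" next to the WAI-S (nurse and patient versions) and the IRI.
- **Analysis.** *Quantitative data analysis* says: "Descriptive statistics will be used for sample description and evaluation of the scores". Before-after differences are tested with a paired t-test or, without normality, a Wilcoxon test. Chi-square or Fisher tests are named for qualitative variables. No covariate enters the WAI-S comparison.
- **Interpretation.** The *Discussion* expects the instruments to demonstrate the change that was produced. *Limitations* concedes the absence of a control group and of randomization, but does not mention patient turnover, case mix or day of stay.

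**The concern.** A nurse's WAI-S score depends on which patients are rated and how long they have been on the ward. If a nurse's patients after the groups differ from those before in diagnosis, age or days since admission, the mean can move without any change in how the nurse works. Pairing by nurse does not protect against this: the nurse is the same, the patients are not. In a one-group design, the measured patient characteristics are among the few available means of separating such a shift from the effect of PAR. The stated test does not use them, and its result is to be read as the change produced.

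**Working it through.** **1. The plan's own figure.** Inputs from *Setting and participants*: two-sided alpha 0.05, power 80%, difference 10, SD 10, loss 10%.

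- Paired, normal approximation: n = ((1.960 + 0.842) × 10/10)² = 7.85, rounded up to 8; 8/0.9 = 8.9, rounded up to 9. This matches the stated nine.
- Two independent groups: 2 × 7.85 = 15.7, so 16 per group; 16/0.9 = 17.8, so 18 per group. This does not match.

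The nine therefore fits a paired single-group calculation, and with 9–10 nurses planned, the nurse is the natural paired unit.

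**2. Can the patients be the same people in both phases?** Before the groups, 9–10 nurses × 30 patients = 270–300 nurse-patient allocations. The Institute has 107 beds in four units. The *Abstract* names two units, which is about 54 beds if units are of equal size (assumption). Even if every patient were shared by three nurses (assumption), 90–100 distinct patients are needed. That is more than about 54 beds, so the sample has to turn over during the first phase alone. Most of these in-patients could hardly be rated again after four group sessions. This is a strong inference, not a statement in the article.

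**3. Size of a spurious shift (all assumed).** Suppose a patient group whose mean WAI-S is 10 units lower changes its share by 10 to 20 percentage points between phases. The shift is 0.10 × 10 = 1 unit to 0.20 × 10 = 2 units.

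**4. Standard error of the paired comparison.** Assume 9 nurses, 30 patients per nurse in each phase (the article gives this only for the first phase) and a total patient SD of 10. ICC is the share of variance between nurses; rho is the correlation of a nurse's effect before and after.

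SD of change in a nurse mean = √(2 × 100 × (1 − ICC)/30 + 2 × 100 × ICC × (1 − rho)); SE = SD/√9.

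| Assumption | SD of change | SE | 1–2 unit shift, in SE |
|---|---|---|---|
| ICC 0.20, rho 1 | √5.33 = 2.31 | 0.77 | 1.3–2.6 |
| ICC 0.05, rho 1 | √6.33 = 2.52 | 0.84 | 1.2–2.4 |
| ICC 0.05, rho 0.5 | √11.33 = 3.37 | 1.12 | 0.9–1.8 |
| ICC 0.20, rho 0.5 | √25.33 = 5.03 | 1.68 | 0.6–1.2 |
| ICC 0.20, rho 0 | √45.33 = 6.73 | 2.24 | 0.4–0.9 |
| SD of 10 taken as SD of nurse-level differences | 10 | 3.33 | 0.3–0.6 |

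The range 0.77 to 1.68 comes wholly from ICC 0.20, with rho moving from 1 to 0.5; rho matters more than ICC.

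**5. False-positive rate with no PAR effect.** Two-sided paired t-test, 8 degrees of freedom, non-centrality 3 × shift/SD, nominal rate 5%:

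- SD of change 2.58 (sampling error only, 10 × √(2/30)): 18% for a 1-unit shift, 53% for 2 units.
- SD of change 5.03: 18% for a 2-unit shift.
- SD of change 10: 5.8% for 1 unit, 8.3% for 2 units.

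**The case against.** - **The second cohort is not stated.** A reader might take the plan to compare one cohort with a later, different one as a matter of record. The article does not say that. Turnover is inferred from the consecutive sampling, the acute setting and the bed count. This stands as a limit on the wording; the inference remains strong.
- **The test is paired.** Each nurse serves as their own control, so stable nurse differences cancel, and unit differences too if nurses stay in their unit. This stands, and unit need not be on the covariate list on that account. It does not answer a change in the patients within a nurse.
- **Description is not said to be the only use.** A reader might infer that the patient variables serve description alone. The article does not say so, and the chi-square or Fisher tests may be meant for categorical characteristics. Even then, a comparison of characteristics would not adjust the WAI-S result.
- **The size is assumed.** This stands. The documents give no case-mix data, ICC or rho. The upper figure of 2.6 standard errors needs perfect nurse correlation and the largest assumed shift, and even 2 units is only 20% of the 10-unit target.
- **Detail may sit in an analysis plan, and limitations are admitted.** A missing covariate list would be no finding in an article. The point is that the comparison the article does state ignores a likely change of patients, which the admitted limitations do not mention. The article also makes the quantitative part complementary to the qualitative one, which lowers the stakes but does not change the inference drawn from the test.

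**Conclusion.** The point holds for the WAI-S, in both the nurse and the patient version. The stated test has no covariates, the day of rating is open beyond day 3, and the patients very probably differ between phases. A case-mix or timing shift can therefore pass as an effect of PAR.

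Its size cannot be fixed from the documents. It may be minor, if the SD of 10 belongs to nurse-level differences, or serious, if nurse means are precise and stable. The article does not say which SD is meant. The documents do not support a claim that the bias is known to be large, or that the plan openly compares two separate cohorts. The change is worth making because most of the data are already to be collected.

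**What to change.** 1. State who the post-PAR patients are, and that the nurse is the paired unit.
2. Record days since admission when the WAI-S is completed, and use the same completion window in both phases.
3. Make the main WAI-S analysis a patient-level model of phase with random effects for nurse and for nurse-by-phase, using small-sample degrees of freedom. Without the nurse-by-phase term, the variance from (1 − rho) is ignored and the standard error is too small. A paired comparison of covariate-adjusted nurse means is an acceptable alternative.
4. Adjust for a short pre-specified list: age, sex, diagnostic group and days since admission.
5. Keep the unadjusted paired test as a sensitivity analysis.

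The cost is analysis wording, two dates per form (admission and completion) and a few degrees of freedom; with 9–10 nurses the list should stay short. Adjustment reduces bias from measured case mix only. Secular trends remain possible in an uncontrolled design, and the report should say so.
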